### Sample size

2.3

To date, there are no studies reporting on the use of deep dry needling and/or percutaneous intratissue electrolysis in patients who have suffered from whiplash syndrome, so that this randomized, blinded clinical trial will provide evidence for the effect size.

To calculate the population size, we used data published by the Directorate General of Traffic (DGT), updated in 2020, which identified 242 patients who were victims of traffic accidents in the city of Melilla. The Al-Therapy Statistics tool will be used for the sample calculation (https://www.ai-therapy.com/psychology-statistics/sample-size-calculator). Therefore, we will use a sample size of (*n* = 36) with a proportional distribution for each study group (GE1 group = 12 + GE2 group = 12 + Control group = 12) with an expected loss ratio (R = 15%) and a confidence interval (CI = 95%), this information is expanded in the Supplementary Material.

However, this calculation does not provide sufficient statistical power. A more robust estimation can be derived from validated clinical parameters reported in the literature: a minimum clinically important difference (MCID) of 2 points on the Numeric Rating Scale (NRS) for pain (151–153), a standard deviation of approximately 2.5 (154), and a pre–post correlation ranging between 0.5 and 0.7 (155, 156). Based on these assumptions, the required sample size would range from 20 to 31 participants per group (60–93 in total) to ensure adequate power.

Since the present study will include only 36 participants, it should be explicitly characterized as a pilot randomized controlled trial, designed to assess feasibility, refine procedures, and provide preliminary effect size estimates to guide the design of a fully powered clinical trial.

For the development of this research, a non-probabilistic intentional sampling will be used for the convenience of the study, due to the characteristics of the subjects to be studied. Strategies to ensure adequate inclusion of participants who meet the target sample size include collaboration with a health center affiliated with the UNESPA agreement on healthcare resulting from traffic accidents, rehabilitation physicians, and physiotherapy teams.

Collaborators will be informed about the study's characteristics during personal interviews and a project presentation. We strive to ensure that patient recruitment reflects sociodemographic diversity in terms of social origin, gender, ethnicity, and education, tailored to the specific characteristics of the reference population in Melilla and with prior information regarding compliance with data protection laws.

### Randomization

2.4

Before patient inclusion, the research team will generate the allocation sequence and randomly assign patients consecutively to GE1, GE2, and the CG. A computerized random number generator will be used. Each participant will be treated separately to prevent any exchange of study information. The nature of the intervention in both groups does not allow blinding of patients and physiotherapists. It is therefore a single-blind study, where the evaluator does not know the nature of the intervention. The evaluator was unaware of the study objectives and the randomized distribution of patients to study groups, and he did not have access to the randomization sequence.

Before patient inclusion, the research team will generate the allocation sequence and randomly assign patients consecutively to GE1, GE2, and the CG. A computerized random number generator will be used. Each participant will be treated separately to prevent any exchange of study information. The nature of the intervention in both groups does not allow blinding of patients and physiotherapists. It is therefore a single-blind study, where the evaluator does not know the nature of the intervention. The evaluator was unaware of the study objectives and the randomized distribution of patients to study groups, and did not have access to the randomization sequence. The evaluator was blinded to treatment allocation throughout the study. Participants were explicitly instructed not to disclose their assigned intervention to the evaluator; treatments and assessments were performed by different staff in separate locations; and any potential unblinding events were systematically logged. At the end of follow-up, the evaluator recorded, for each participant, their guess of allocation (active/sham/don't know), allowing for a quantitative evaluation of blinding success.

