### Intervention

2.5

Study subjects are randomly assigned to one of the following three groups: Experimental Group 1 (EG1), Experimental Group 2 (EG2) or the Control Group (CG) through a computer randomization system using the statistical program Epidat V4.2.

Once the subjects have been informed of the entire study procedure and have signed the informed consent form (Annexes I, II) this information is expanded in the Supplementary Material, they will be evaluated before starting treatment. Subjects will receive an initial evaluation based on clinical parameters and follow-up medical records. The data will be collected by an evaluator and integrated into our research databases using an Excel spreadsheet.

Both experimental groups will receive an invasive physiotherapy protocol (one weekly session) applied to the sternocleidomastoid and/or levator scapulae muscles, in addition to the standard physiotherapy program. The intervention will be conducted over four weeks, with a total of 20 sessions (five per week), following rehabilitation medicine guidelines for this condition. This standardization ensures consistency in treatment exposure and enhances reproducibility of the protocol.

The therapeutic exercise program will be delivered under the supervision of trained physiotherapists. Exercises will be performed in progressive phases, with adjustments in intensity, resistance, and volume according to predefined progression criteria. Details of the exercise program are summarized in Table 1.

**Table 1 T1:** Relationship between standard physiotherapy procedure and intervention.

Intervention procedure	Physiotherapy intervention	Description	Duration/Repetitions	Frequency	Subjects
Experimental group	EPI	Hong technique on localized MTrPs (ECOM and/or Levator scapulae)	1× week	1 day for 4 weeks	GE_1_
	Dry needling	Hong technique on localized MTrPs (ECOM and/or Levator scapulae)	1× week	1 day for 4 weeks	GE_2_
Standard physiotherapy procedure (GE + GC)	Thermotherapy + analgesic electrotherapy	Microwave or thermotherapy techniques combined with TENS.	15 min	5 days for 4 weeks	GE + GC
	Massage therapy	Friction maneuvers, kneading, and manual stretching of the muscle and affected area.	20 min	5 days for 4 weeks	GE + GC
	Manual therapy	- Deep friction massage - Contraction- relaxation technique passive - Stretching and self-stretching	10 min	5 days for 4 weeks	GE + GC
			2–3 repetitions		

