### Outcomes measures and tools

2.6

The initial assessment includes a clinical history-taking interview. We will strive to ensure the sample data are homogeneous at the start of the study, ensuring there are no significant differences in demographic, medical, and other variables at the outset.

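### One team generates the list and assigns patients, nothing places assignment after consent and baseline, and baseline non-significance is an aim that randomisation cannot guarantee

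*Protocol article*

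**What the plan says.** Section 2.4 (Randomization) prints the same statement twice: "Before patient inclusion, the research team will generate the allocation sequence and randomly assign patients consecutively to GE1, GE2, and the CG". On method it adds "A computerized random number generator will be used", and section 2.5 (Intervention) says assignment is made "through a computer randomization system using the statistical program Epidat V4.2". The one person excluded from the list is the evaluator, who "did not have access to the randomization sequence". On masking, section 2.4 says "The nature of the intervention in both groups does not allow blinding of patients and physiotherapists".

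Section 2.5 opens with random assignment to the three groups. Its next paragraph begins "Once the subjects have been informed of the entire study procedure and have signed the informed consent form" and goes on to an evaluation that has to precede treatment. It does not say that this evaluation precedes assignment.

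Section 2.3 (Sample size) fixes the arms as "GE1 group = 12 + GE2 group = 12 + Control group = 12" and describes recruitment as intentional, non-probabilistic sampling. Section 2.6 (Outcomes measures and tools) says the team will try to make the sample homogeneous at the start, "ensuring there are no significant differences in demographic, medical, and other variables at the outset".

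**The concern.** Two separate protections are needed. Masking the evaluator protects outcome measurement. Concealing the next assignment from whoever decides on entry protects the composition of the arms. The article states the first and gives wording that works against the second: the same team makes the list and assigns from it, and nobody except the evaluator is kept away from it.

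If those who recruit can see the next assignment, they can hasten, delay or decline an entry because of it, and a patient who already knows the arm can decline. Baseline NRS and WDQ are self-reported, so a patient who knows the arm may score differently, and masking the evaluator does not correct a self-report. Adjusting for a baseline score affected in this way would carry the distortion into the analysis.

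The aim in section 2.6 adds pressure. A team that can see the list and wants no significant differences at the outset has a reason to influence entry, and the article names no legitimate device for balance, such as stratification or minimisation.

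**Working it through.** The plan gives no figure on concealment. Its only relevant number is the group size, 12 + 12 + 12 = 36. The main check is therefore a reading of the text, followed by three short calculations.

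**Reading the text**

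| Question | What the article states |
|---|---|
| Who makes the list? | The research team (2.4) |
| Who assigns? | The research team (2.4) |
| Who is kept from the list? | The evaluator only (2.4) |
| When is consent? | Described after assignment (2.5), with no word fixing the order |
| When is baseline? | Before treatment (2.5); not stated as before assignment |
| Do patients know their arm? | They are not blinded (2.4) |
| Who chooses the patients approached? | Intentional sampling (2.3) |

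No statement separates the list-holder from those who enrol, and none puts assignment after consent and baseline.

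**1. Can randomisation deliver the aim in section 2.6?**
Inputs: a 5% level (section 2.7) and k independent baseline comparisons. The article does not give k, so 5 to 10 is an assumption. The chance of at least one significant difference under correct randomisation is 1 − 0.95^k.
- k = 5: 1 − 0.95^5 = 0.226
- k = 8: 1 − 0.95^8 = 0.337
- k = 10: 1 − 0.95^10 = 0.401

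The aim would fail by chance in 23% to 40% of properly randomised trials. Correlated variables would change these figures somewhat.

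**2. How predictable is the next assignment?**
Take one random list with fixed totals of 12 per arm, and a person who sees only past assignments and always guesses the arm with most places left. Over 10,000 simulated lists that person is right 16.1 times in 36, against 36/3 = 12 by pure guessing. With blocks of 3, the first, second and third places are guessed with probability 1/3, 1/2 and 1. That is 1/3 + 1/2 + 1 = 11/6 per block, and 12 × 11/6 = 22 of 36. A person who holds the list knows all 36. Access to the list is the main exposure, but small blocks would also be a poor remedy here, where therapists see the assignments.

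**3. Is the stated method compatible with 12/12/12?**
If assignment were unrestricted 1:1:1, P(12, 12, 12) = 36!/(12!³ × 3^36) = 0.0226. In 500,000 simulated trials the smallest arm had 8 or fewer in 31.2%. Fixed arms of 12 therefore imply a restricted list. These two figures apply only to an unrestricted scheme, which the article does not specify.

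**The case against.** The best defence is that an article condenses. The SPIRIT checklist is in supplementary material and the flow chart is not shown, so a concealment device may be described there. The opening phrase about inclusion may govern only the making of the list, which is normal practice, and patients can hardly be assigned consecutively before they are included. A research team is a collective, so the list-holder need not be the recruiter.

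Much of this stands, and it limits what can be claimed. A reader might infer any of the following, and the documents do not support them:
- **Patients are allocated before consent.** This rests on syntax and paragraph order; no sentence says it.
- **Eligibility is confirmed after allocation.** The palpation in section 2.7 is described together with the measuring instruments. An active trigger point is already an inclusion criterion in section 2.2.
- **The team promises balance and can reach it only by steering.** The sentence in section 2.6 is worded as an effort, and stratification or minimisation pursues balance legitimately.
- **The generator is unrestricted, so 12/12/12 will rarely occur.** A computer generator can produce a blocked or fixed-total list.
- **Intentional sampling biases the arms.** It concerns who is recruited. It matters only where the next assignment is visible.
- **A few steered entries could create or cancel an effect.** No figure supports this. With 12 per arm and the SD of 2.5 in section 2.3, swapping one patient for another one SD away moves the arm's mean NRS by 2.5/12 = 0.21, about a tenth of the 2-point difference cited there.

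The defence does not answer the affirmative wording. Generation and assignment are given to the same team, only the evaluator is excluded, and baseline is timed against treatment when it should be timed against assignment. Supplementary detail could add a device, but these sentences would still need correcting.

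**Conclusion.** The point holds as a defect in what the article states. Followed as written, the procedure does not protect allocation from those who enrol, and it lets baseline NRS and WDQ be recorded from patients who know their arm. Selective entry could affect every outcome, including the two primary imaging measures. The self-report problem affects the pain and disability scores. The size of any bias cannot be calculated from the article, and there is no evidence that steering is intended.

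The aim of no significant baseline differences is unsound regardless of concealment: it would fail by chance in 23% to 40% of correctly run trials, assuming 5 to 10 independent tests at 5%. That the trial calls itself a pilot does not remove the problem, since section 2.3 intends its effect estimates to guide a larger trial, and analysis cannot reliably undo allocation bias.

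**What to change.** 1. In sections 2.4 and 2.5, state one order: eligibility, consent, baseline measurement with patient and evaluator both unaware of the arm, then allocation.
2. Have the list made and held by existing staff who do not recruit, treat or assess. Release each assignment only once baseline is recorded, from a locked file or sealed opaque envelopes.
3. State that the list is restricted to give 12 per arm. Use varying block sizes in multiples of 3, larger than 3 and summing to 36, not disclosed to those who recruit or treat.
4. Replace the balance sentence in section 2.6 with descriptive reporting of baseline by arm, without significance tests, and adjust each outcome analysis for its baseline value whatever balance is seen.
5. If enrolment has begun, record who held the list and when each assignment was released relative to consent and baseline.

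The cost is a few sentences and some administrative handling of the list. The baseline values are already to be collected. The one practical condition is that the centre can name someone outside recruitment, treatment and assessment; the article does not identify such a person.

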**Methods:**

This single-blind randomized clinical trial will be conducted in patients residing in Melilla with whiplash syndrome due to traffic accidents. Participants will receive interventions targeting the sternocleidomastoid and/or levator scapulae muscles. Assessments will be conducted at baseline, after four weeks of intervention, and at three months post-intervention to evaluate medium-term effects. Our hypothesis is that EPI will produce greater improvements in the study variables compared to DN and standard physiotherapy.

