**Figure 2 F2:**
[figure not shown]
EPI Model: XM Omega.

In the case of dry needling treatment on a myofascial trigger point located in the sternocleidomastoid and/or levator scapulae muscles of the affected area, the aforementioned asepsis and hygiene measures must also be followed beforehand.

The modified Hong technique (quick entry and exit) is performed, seeking a local spasm response—at least one response, indicating that the treatment is more effective than without it (62). Once the needle is withdrawn, pressure should be applied to the puncture site where the technique was performed for 1–2 min to prevent bruising. This is done as post-needle care to prevent post-needle pain and promote hemostasis.

The procedure at the control group will include standard physical therapy following the progression criteria based on clinical guidelines for patients with whiplash syndrome (14), treating the sternocleidomastoid and/or levator scapulae muscles with a frequency of 5 weekly sessions for 4 weeks. The two professionals performing the procedure are professionals with more than ten years of experience in invasive techniques. Before the start of the trial, the therapists participated in a training and protocol standardization session to ensure consistency in the application of the procedures. Treatment fidelity measures were implemented throughout the study, and any protocol deviations were systematically recorded. The professionals and evaluators are different.

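### The evaluator's blinding guess (*active*, *sham*, *don't know*) does not match the three arms, so the blinding check is not interpretable as specified and cannot test EPI against dry needling

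*Protocol article*

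**What the plan says.** Section 2.4 (Randomization) makes the evaluator the only blinded party: "The nature of the intervention in both groups does not allow blinding of patients and physiotherapists". To check that this blinding held, "the evaluator recorded, for each participant, their guess of allocation (active/sham/don't know), allowing for a quantitative evaluation of blinding success". The same section adds other protections: participants are told not to reveal their treatment, treatment and assessment use different staff and places, and possible unblinding events are logged.

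Section 2.5 (Intervention) gives the design: "Study subjects are randomly assigned to one of the following three groups", namely EG1, EG2 and CG. "Both experimental groups will receive an invasive physiotherapy protocol (one weekly session"), on top of the standard programme; Table 1 shows EPI for the first group and dry needling for the second. For the third arm, "The procedure at the control group will include standard physical therapy following the progression criteria based on clinical guidelines". Table 1 lists its content as thermotherapy with TENS, massage, manual therapy and active mobility. Section 2.3 gives the arm sizes: "GE1 group = 12 + GE2 group = 12 + Control group = 12".

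The Abstract states the hypothesis: "Our hypothesis is that EPI will produce greater improvements in the study variables compared to DN and standard physiotherapy".

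**The concern.** The response options suit a two-arm, sham-controlled trial. This trial has three arms, none of them a sham, and its comparator is a real treatment given five times a week. Apart from the guess form, the article does not mention a sham, and it refers to placebo only in the Introduction when describing other studies. Nothing says which label is the correct answer for a participant in EG1, EG2 or CG.

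What is at stake is the formal check on the trial's only blinding. Sections 2.6.1 and 2.7 have the evaluator take the primary measurements, Doppler ultrasound and elastography, in tissue that has been needled in two arms and not in the third. Section 2.5 itself mentions possible bruising after needling and an inflammatory response after EPI lasting 5 to 7 days and at most 15. Whether such signs would still be present at the post-treatment visit depends on its timing, but a guess form is meant to find out whether the evaluator could tell the arms apart. This one cannot record a guess that distinguishes the two needling arms.

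**Working it through.** The plan gives no figure here and names no index, so there is nothing to reproduce. The check compares the labels with the arms and then works through an index on the planned numbers.

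**Inputs.** Labels: *active*, *sham*, *don't know* (section 2.4). Arms: EPI plus standard, dry needling plus standard, standard only (section 2.5 and Table 1). Size: 12 per arm, 36 in total (section 2.3). Assumption for illustration: Bang's index, computed per arm as

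BI = (correct guesses − wrong guesses) / number in the arm.

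**Reading (a): labels taken literally.** All three arms receive active treatment, so 12 + 12 + 12 = 36 participants are *active* and 0 are *sham*.

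- Sham arm: the denominator is 0, so BI is undefined.
- If every guess is *active*, BI = (12 − 0)/12 = 1.0 in each arm, whatever the evaluator knows.

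The index is therefore undefined for one label and uninformative for the other.

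**Reading (b): *active* = EPI or dry needling, *sham* = control.** The article does not state this mapping. It gives 24 needled and 12 control participants.

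| Evaluator's state of knowledge | BI, needled (24) | BI, control (12) |
|---|---|---|
| Knows all three arms exactly | (24 − 0)/24 = 1.0 | (12 − 0)/12 = 1.0 |
| Knows only needled versus not needled | (24 − 0)/24 = 1.0 | (12 − 0)/12 = 1.0 |
| Says *active* at random two thirds of the time (expected counts) | (16 − 8)/24 = +0.33 | (4 − 8)/12 = −0.33 |
| Always says *active* | (24 − 0)/24 = +1.0 | (0 − 12)/12 = −1.0 |

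Under this reading the index works for needling versus no needling: perfect knowledge (1.0 and 1.0) differs from random guessing (+0.33 and −0.33) and from a constant answer (+1.0 and −1.0). The first two rows are identical, so the index cannot show whether the evaluator could tell EPI from dry needling.

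**Does splitting the needled group help?** Tabulating the guesses separately for EPI and dry needling changes nothing: an evaluator who knows all three arms answers *active* for all 12 in each, and so does one who knows only that a needle was used. The missing information is not on the form, so no later analysis can recover it.

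**The case against.** The strongest reply is that the intended meaning is easy to guess: *active* for the experimental groups and *sham* for the control group. A needled-versus-control index then exists. The last paragraph of the Introduction also words the primary objective as both needling techniques against the standard protocol, which is the contrast this index would address. The choice of index could be left to an analysis plan that is not shown.

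Much of this stands. A reader might infer that no blinding statistic can be computed at all; reading (b) shows that one can. What the reply does not cover is EPI against dry needling. The Abstract's objective and hypothesis both name that contrast, and an analysis plan can add a mapping but not a guess that was never recorded.

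Other stronger readings are tempting and are not supported:

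- **Opposite conclusions from the same data.** An all-*active* response scores 36/36 correct if standard care counts as active and 24/36 if it counts as sham. These are raw percentages, not a blinding index. A constant answer shows no discrimination under either coding, so neither figure indicates unblinding.
- **A wrong chance level.** The article states no chance level, so there is none to correct.
- **A guess taken too late.** The article names no primary time point. The Abstract has a three-month visit, while section 2.7 lists only a pre-test and a post-test, so it is not established that the guess follows the primary assessment.
- **No evidence on blinding at all.** The log of unblinding events in section 2.4 does not depend on the guess form.

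**Conclusion.** The point holds in a limited form. The response options do not match the three arms, no rule links them, and the promised quantitative evaluation is not interpretable as specified. At best, under an unstated mapping, it yields an index for 24 needled against 12 control participants. It gives no information on blinding between EPI and dry needling.

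The mismatch follows from the article's own text. Only the illustration rests on assumptions: Bang's index, full recruitment of 12 per arm, and the mapping in reading (b).

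The consequence is confined to the blinding check. Sample size and primary analysis are unaffected. Nothing here shows that the evaluator was or will be unblinded; the safeguards and the log in section 2.4 stand. The correction is still worth making, because section 2.3 presents the study as a pilot meant to refine procedures and this is the formal check on its only blinding.

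**What to change.** In section 2.4 and on the case report form, replace the options with: EPI, dry needling, standard physiotherapy only, don't know. Report a blinding index per arm and two tabulations: needling versus no needling in all 36, and EPI versus dry needling in the 24 needled participants.

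State how the index is defined for three named arms and what value corresponds to guessing. If (correct − wrong)/n is kept and guesses are spread evenly over three arms, the expected value is (4 − 8)/12 = −0.33 in each arm, not 0.

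Section 2.4 describes the guess in the past tense. If guesses have already been collected on the old form, write down which arms *active* and *sham* stand for, report the needled-versus-control result only, and say plainly that blinding between EPI and dry needling was not tested.

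The cost is one line on the form and one table in the report.
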